#### Statistical Methods

2.7.2

Analyses will follow a pre‐defined statistical analysis plan on an intention‐to‐treat basis, with two‐sided tests and a significance level of *α* = 0.05. Descriptive statistics will summarize socio‐demographic, clinical, and health profiles. Categorical data will be presented as frequencies and compared using chi‐square tests, reporting odds ratios and 95% confidence intervals. Continuous variables will be presented as either mean with standard deviation or median with interquartile range, with group comparisons via independent *t*‐tests or Mann‐Whitney *U* tests as appropriate.

Primary and secondary endpoints between groups at 12 months will be analyzed using mixed‐effects models, adjusting for baseline values and relevant socio‐demographic confounders, to assess treatment effects over time. Implementation objectives will be evaluated using a mixed methods approach: a 19‐question survey (including two free‐text sections) and focus groups (5–10 participants per intervention group), with qualitative data analyzed thematically.

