#### Sample Size Calculation

2.7.1

The sample size was determined based on the objective to compare progression rates across the three groups. A total of 30 participants per treatment group (total *n* = 90) is required to undergo serial, evaluable imaging. This sample size provides 80% power to detect a difference in the progression of non‐calcified plaque volume between a pair of groups of 8 mm^3^, assuming a standard deviation of 11 mm^3^, a Bonferroni‐adjusted alpha of 0.83%, and that baseline adjustment accounts for one‐third of outcome variability.

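### The article sizes the primary pairwise comparisons at a Bonferroni-adjusted 0.83% but gives 0.05 for the analysis without saying whether that is the family-wise or the per-comparison level

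*Protocol article*

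**What the plan says.** Section 2.7.1 of the Protocol article asks for 30 participants per arm (90 in total) with evaluable serial imaging. It states: "This sample size provides 80% power to detect a difference" in progression of non-calcified plaque volume "between a pair of groups of 8 mm^3", "assuming a standard deviation of 11 mm^3", with a Bonferroni-"adjusted alpha of 0.83" per cent, and on the footing that "baseline adjustment accounts for one"-third of the outcome variability. It does not say how many comparisons the Bonferroni division covers, or whether 0.83% is one-sided or two-sided.

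Section 2.7.2 says that a pre-defined statistical analysis plan will be followed, by intention to treat, with two-sided "tests and a significance level of" 0.05. Primary and secondary endpoints go to mixed-effects models adjusted for baseline. The section names no primary contrast, no global test, no order of testing and no multiplicity adjustment. It neither repeats the 0.83% nor describes 0.05 as an overall level.

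**The concern.** Three arms allow three pairwise comparisons on the primary endpoint. The article gives one threshold for designing the trial and another for analysing it, and nothing links them. A pairwise p-value between 0.0083 and 0.05 could be called a success or a failure depending on which section is followed.

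Recruitment closed with 79 randomised (26, 27 and 26) against 90 evaluable participants required, so power at 0.83% is already below the planned 80%. That makes the choice of threshold more likely to matter, and more awkward to settle once results are known.

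**Working it through.** **Inputs.** From 2.7.1: difference 8 mm³, SD 11 mm³, one-third of variance explained by baseline, alpha 0.83%, power 80%, 30 per arm. From 2.7.2: two-sided, 0.05. From Participants (2.2): 26, 27 and 26 randomised.

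**1. The plan's own figure.**
- Residual SD = 11 × √(1 − 1/3) = 8.98 mm³.
- n per arm = 2 × 8.98² × (z₁₋α/₂ + z₀.₈₀)² / 8². With two-sided α = 0.0083, this is 2 × 80.67 × (2.640 + 0.842)² / 64 = 30.6, so 31 against 30 stated.
- Power at 30 per arm is 79.1% by the normal approximation and about 77% with the t distribution.
- The same formula gives 27 per arm at 1.67% and 20 per arm at 0.05.

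The stated size fits a two-sided 0.83% test closely. The stricter level therefore drove the sample size.

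**2. Where 0.83% could come from.** 0.05/3 = 1.67%. 0.05/6 = 0.83%, and 0.025/3 = 0.83%. Three two-sided comparisons under a family-wise 0.05 do not produce it. Either six comparisons are counted, or 0.025 is divided by three. If 0.83% is a one-sided level, it equals 1.67% two-sided, and 30 per arm would give about 85% power instead of the stated 80%.

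**3. Family-wise error when no arm differs.** For three equal arms, the chance that at least one pair is significant is 1 − F(t × √2; 3, df), where F is the studentized range distribution and t the two-sided critical value. With t = 1.960 this is 12.2%; with df = 79 − 4 = 75 it is 12.1%. The simpler 1 − 0.95³ = 14.3% overstates it, because the pairs share arms. Simulation at 26/27/26, with residual SD 8.98 and df 75, gives:

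| Rule | Family-wise error |
|---|---|
| Three pairs, each at 0.05 | 12.1% |
| Two comparisons with control, each at 0.05 | 9.0% |
| Three pairs, each at 1.67% | about 4.4% |
| Three pairs, each at 0.83% | about 2.2% |
| Global 2-df test at 0.05, then pairs at 0.05 | 5.0% |

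**4. Power for one 8 mm³ pair at 26/27/26.** This assumes that everyone randomised has an evaluable second scan. The article reports numbers randomised and no follow-up numbers, so these are upper values.

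| Rule | Power |
|---|---|
| Pair at 0.05, unadjusted | 89% |
| Global test first, third arm equal to one of the pair | 86% |
| Global test first, third arm midway | 81% |
| Pair at 1.67% | 78% |
| Pair at 0.83% | 69% |

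With a true 8 mm³ difference, that pair's p-value falls between 0.0083 and 0.05 in about 89 − 69 = 20% of trials. With no true difference, the smallest of the three p-values falls there in about 12.1 − 2.2 = 10%.

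**The case against.** The strongest reply is that the two sections need not conflict. A Bonferroni-adjusted level implies a parent level, and the 0.05 in 2.7.2 may be that parent, with 0.83% applied to each pair. The sentence in 2.7.2 introduces all the analyses, including secondary ones where a nominal 0.05 is ordinary. It also points to an analysis plan that is not shown and may hold the rule. The stated aim of comparing progression across three groups is compatible with a global test first.

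Much of this stands. A reader might infer that the trial will test each pair at 0.05 without adjustment and so has a 12% family-wise error. The document does not support that. It is silent on adjustment and does not deny one, and it does not say that 0.05 applies to each pair or that all three pairs are primary. The error is about 9% if only the two control comparisons count and 5.0% with a global test first. Nor is it established that the sections set two rival success criteria.

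What does not stand is that the parent-level reading settles the matter. Three two-sided comparisons under 0.05 give 1.67%, not 0.83%, and no passage explains the factor of six or the division of 0.025. The point is also more than detail left to the analysis plan, because the article itself prints both levels and leaves their relation open.

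**Conclusion.** The point holds as an ambiguity in the primary success rule, at should-fix level. Neither reading of 0.05 fits 2.7.1 as written. Per comparison, it drops the adjustment on which the trial was sized and gives a family-wise error of about 12% (three pairs) or 9% (two comparisons with control). Family-wise, it makes 0.83% stricter than three two-sided comparisons require, with an actual error of about 2.2%; for an 8 mm³ pair, power is then 69% against 78% at 1.67%.

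The error figures assume that no arm differs. The power figures assume the article's SD and baseline adjustment, and no dropout from the 79 randomised. The unseen analysis plan may already contain a clear rule; if so, the article only needs to agree with it.

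**What to change.** Before unblinding, state in 2.7.2 that 0.05 is the two-sided family-wise level for the primary endpoint, list the primary contrasts, and give one rule:

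- **Bonferroni, carried over explicitly.** Either keep 0.83% per pair as planned and say how it was derived, or use 1.67% if three two-sided comparisons are meant. Keeping 0.83% changes nothing in the plan, at the price of lower power.
- **Closed procedure for three groups.** Test the 2-df arm effect in the baseline-adjusted model at 0.05, and test each pair at 0.05 only if that is significant. With exactly three arms, any two true pairwise nulls imply the global null, so this controls the family-wise error strongly, at 5.0%. Its gain over Bonferroni at 1.67% is about 3 points if the third arm lies midway (81% against 78%) and about 8 points if it equals one of the pair (86% against 78%).

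Either option costs one paragraph. The closed procedure allows no pairwise claim when the global test fails. It, or a move to 1.67%, would also relax the planned per-pair threshold after recruitment has ended, so the change and its reason must be documented as made before unblinding. The same rule should appear in the analysis plan.

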### Ethics and Governance

2.8

#### Ethics Approval

2.8.1

The study complied with the National Statement on Ethical Conduct in Human Research by the Australian National Health and Medical Research Council (National Health and Medical Research Council, 2018) and was approved by Monash University Health Research Ethics Committee (Project number: RES‐22‐0000‐656A).

#### Data Management

2.8.2

Participant data were stored in an encrypted, secure electronic database (REDCap) hosted by Monash University. with access limited to authorized staff. Data were de‐identified for analysis, and records will be retained for 15 years in accordance with guidelines.

#### Trial Registration

2.8.3

ClinicalTrials. gov ID: NCT07091162.

## Discussion

3

The VOLTAIRE trial is one of the first studies to evaluate the impact of personalized cardiovascular risk information, derived from CTCA and PRS, on cardiovascular risk factor modification. While effective communication is known to motivate behavioral changes and improve adherence, the specific impacts of CTCA and PRS in these areas remain underexplored.

Providing patients with vascular plaque information via carotid ultrasound or coronary artery calcium (CAC) imaging can improve risk factor control and medication adherence [11, 33]. However, carotid ultrasound assesses only the carotid arteries, and CAC detects only calcified plaques, potentially missing non‐calcified, vulnerable plaques [9]. By contrast, CTCA visualizes both calcified and non‐calcified plaques, offering a more comprehensive evaluation of CAD [9, 29]. Despite these advantages, evidence on CTCA's ability to drive behavioral change is mixed, likely due to differences in communication, reinforcement, and whether patients received their images [19].

PRS is an emerging tool for identifying genetic predisposition to CAD, with high genetic risk typically conferring a two‐ to threefold higher relative risk than average [27]. Despite this, adherence to a healthy lifestyle can significantly mitigate risk. Khera et al. showed that high‐risk individuals maintaining favorable lifestyles had a 46% lower relative risk of coronary events [27]. Yet, behavioural effects of PRS has been mixed, largely due to differences in communication [21, 34]. A recent systematic review suggests that genetic insights may prompt modest dietary improvements but has little effect on physical activity, medication adherence, or traditional risk factors [35]. To address these challenges, a key recommendation is to contextualize genetic risk by using visual aids [36, 37]. The VOLTAIRE trial adopts this approach, presenting PRS via a bell curve to enhance comprehension and support informed decision‐making.

In addition, VOLTAIRE was designed to address limitations of prior imaging and genetic risk disclosure studies through co‐designed visual reports, structured nurse‐led counseling, personalized recommendations, and reinforcement at follow‐up. CTCA and PRS reports were developed in partnership with hospital consumer representatives, using simple language and visual summaries, to ensure relevance and accessibility. Acceptability and effectiveness will be further evaluated through focus groups.

The VOLTAIRE trial also addresses broader health needs by screening for depression, anxiety, diabetes distress, and sleep apnoea, with referral of severe cases to GPs. This integrated approach recognizes the interplay between physical and psychological health. Recruitment through community GP clinics, diabetes support groups, social media, and local university campuses supported enrollment of a broader and more diverse cohort.

This study should be interpreted considering several limitations. The single‐center design may limit generalizability to other populations and settings, and hospital‐based enrollment may still have preferentially included individuals who were more engaged with healthcare, which could have influenced responsiveness to the interventions. Given the open‐label design, performance bias cannot be excluded, as participants and clinicians were aware of group allocation. The modest sample size was powered for the primary mechanistic endpoint but may have limited statistical power for some secondary and exploratory outcomes. Larger, adequately powered multicentre studies are needed to confirm these findings.

## Data Availability

Data sharing not applicable to this article as no datasets were generated or analyzed during the current study.
